#### Concealment mechanism {16b}

Randomization is performed centrally at the Clinical Trials Unit in order to guarantee therapy allocation confidentiality. If a participant has given his or her written consent, then the participant’s identification code, year of birth, sex and confirmation that inclusion/exclusion criteria are fulfilled will be sent by fax to the central randomization office at the Clinical Trials Unit for randomization. To maximize therapy-uptake rates, all participants are screened and subsequently randomized as close as possible to the available therapy dates.

#### Implementation {16c}

The allocation sequence was generated by a statistician of the Clinical Trials Unit not involved in study planning or conduct. After receiving the randomization results from the Clinical Trials Unit, the investigators inform the participants about their group assignment by telephone and provide information regarding admission into their respective therapy groups.

### Assignment of interventions: blinding

#### Who will be blinded {17a}

Given the characteristics of the study, the therapists who conduct the smoking cessation therapies cannot be blinded to the study condition. Biochemical verification of the abstinence status will be conducted blind to the randomization arm. Data analysts have access to the trial database and, therefore, are not blinded. The statistical methods for the final analysis were prespecified.

#### Procedure for unblinding if needed {17b}

Not applicable due to an unblinded study design.

### Data collection and management

#### Plans for assessment and collection of outcomes {18a}

Self-report data will be collected using standardized questionnaires in a secure encrypted online-based assessment system. Standardized observer-based assessments will be conducted via telephone by trained interviewers.

#### Plans to promote participant retention and complete follow-up {18b}

To maximize retention, participants receive financial reimbursement as well as a reminder of therapy commencement and are contacted by telephone and email for all assessments. Moreover, telephone interviews are scheduled, if possible, and participants can choose from different methods of completing the questionnaires.

Participants may withdraw from the study for any reason at any time. Reasons for dropout will be protocolled, if possible.

#### Data management {19}

All relevant study data are collected on electronic CRFs (eCRF) using the system REDCap (Research Electronic Data Capture, https://www.project-redcap.org/), browser-based electronic data capture software.

The electronic forms were developed and validated for completeness and correctness of formats, branching logic and edit checks by the data management team at the Clinical Trials Unit. A user acceptance test was performed by the CCCF study team.

Data entry is done by CCCF study staff. Additionally, participants can choose to fill out their questionnaires either on paper or directly into the eCRF. Access to the eCRF is regulated by personal data entry user profiles with limited rights for CCCF study staff, and directly by the personal email address entered in a special master file form for the participants. Participants’ access is managed by CCCF study staff and is limited to the respective periods of time.

Data entry and data corrections on e-forms are automatically tracked in the audit trial created by the eCRF system. All data collected during the trial are entered as timely as possible. Reports and standard dashboards assist CCCF study staff in monitoring progress of data entry. The survey tool supports reminders for participants who do not fill out their questionnaires in a timely manner.

#### Confidentiality {27}

Personal data necessary for conducting the study are shared only with the prevention team of the University Medical Center Freiburg that conducts the study. All online assessments are protected using an encrypted connection to prevent unauthorized access by third parties. Data for the statistical evaluation will be pseudonymized and electronically processed for analysis, which will be carried out by staff of the University Medical Center*.* All data obtained are handled in accordance with the legal data protection regulations and the guidelines of the University of Freiburg ethics committee. In line with the recommendations of the data-protection supervisor of the University Medical Center Freiburg and the *Guidelines for Safeguarding Good Scientific Practice* of the DFG, anonymized data will be archived for 10 years on a secure institutional storage medium [89].

#### Plans for collection, laboratory evaluation and storage of biological specimens for genetic or molecular analysis in this trial/future use {33}

Cotinine values will be determined with liquid chromatography–mass spectrometry (LC-MS/MS) to validate the non-smoking status after 12 months. The procedure has been developed and validated by MVZ Clotten Laboratory Freiburg (Freiburg im Breisgau, Germany), which will analyze all samples. MVZ Clotten is not otherwise related to the trial. Urine sample kits including detailed instructions on collection and dispatch will be sent to all participants stating that they have stopped smoking. About 10 ml of urine will be collected from each participant and all samples will be sent immediately by post to MVZ Clotten. To avoid misclassification of abstainers and passive smokers as actively smoking, a cutoff value of 250 ng/ml urine will be used as the baseline to identify active smokers [90, 91]. Due to unclear scientific evidence, no adjustments for creatinine concentration will be made [92, 93]. Cotinine will be stored at − 80 °C for 6 months to allow for plausibility checks prior to disposal.

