##### Intervention group

A residential behavioral group therapy program consisting of 10–12 participants is conducted over a 9-day period at the Breisgau Klinik. The methodical basis for this smoking cessation therapy is motivational interviewing, as described by Miller et al. [46]. This comprises the evidence-based behavioral smoking cessation therapy ‘Rauchfrei in 6 Wochen’ [37], which includes: preparation for abstinence (information about physical and psychological functionality of tobacco dependence, dealing with craving and withdrawal symptoms, motivational support to make a reasoned decision to quit smoking); the termination of tobacco consumption in the group (stimulus control, training of behavioral alternatives); and relapse prevention (adopting health-promoting behavior, relaxation training, social support, dealing with risk factors and relapses). It is flanked by supportive activities such as therapeutic exercise, relaxation techniques and nutrition counseling. Six sessions of smoking cessation therapy, lasting 1.5 h each, are performed only by trained and certified therapists of the Comprehensive Cancer Center Freiburg (CCCF), University Medical Center Freiburg. Supportive interventions are provided by qualified personnel belonging to the Breisgau Klinik. Beyond the smoking cessation sessions, participants take part in planned activities and general routines established by the rehabilitation clinic. In accordance with scientific recommendations [17] and present clinical guidelines for outpatient smoking cessation [16], participants receive advice on the use of stop-smoking aids and licensed medication to alleviate withdrawal symptoms. Use of stop-smoking aids and medication is voluntary. To increase treatment adherence, participants in the residential group are required to pay a study contribution of €50.

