### Measures

#### Primary endpoint

The 6-month and 12-month continued smoking abstinence will be assessed in accordance with international Russell Standard criteria via categorical questions [56]: participants will be classified as abstinent if they smoke no more than five cigarettes during the observation period. In an intention-to-treat analysis, participants lost to follow-up will be counted as relapsed. A recent multicenter trial has shown that, after smoking cessations, there is a high risk of participants inflating their abstinence rates in self-reports when compared to biochemical verification [61]. Hence, abstinence will be validated by urine cotinine assessments at the 12-month follow-up. Urine cotinine is the most widely used biomarker in smokers as it is more sensitive than blood cotinine, non-invasive [62, 63] and can specifically distinguish between first-hand and second-hand tobacco exposure [64].

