##### Aids for abstinence

Intake and period of usage of different kinds of stop-smoking aids as supporting agents for tobacco abstinence will be investigated following therapy, after the 6-month and 12-month follow-ups. Assessments include medications authorized in Germany, such as nicotine patches, gums, sprays, sublingual tablets or other inhalants as well as bupropion (Zyban) and vareniclin (Champix). Additionally, the use of e-cigarettes will be evaluated. Results from a recent study suggest that e-cigarettes could significantly help in quitting the smoking of tobacco. In contrast, caution is advised because the long-term use of e-cigarettes indicates an addiction shift rather than actual abstinence from smoking [59]. Due to a lack of information on long-term health risks and new reports on vaping-induced lung injury, e-cigarettes are not primarily advised as a stop-smoking aid [66]. Use of e-cigarettes is critically discussed as a means of harm reduction, based on preliminary evidence available for either of the therapies [67]. We will assess the use of e-cigarettes and conduct analyses of this subgroup of participants in comparison to those using other stop-smoking aids.

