### Sample size {14}

The sample size calculation is based on nicotine abstinence after 6 months as the primary endpoint of the trial. According to Hays et al. [21, 38] and clinical experiences in cooperation with our local network for smoking cessation, 6-month abstinence rates of ≈ 27% from outpatient smoking cessation under routine conditions are expected. At a two-sided significance level of α = 5%, the null hypothesis of equality of abstinence probabilities in both groups should be rejected with a power of 90%, if the residential program increases the abstinence probability to 50%. To date, no data on dropout rates for prospective controlled studies on residential smoking cessation are available. Therefore, estimations of dropout rates are based on published studies on outpatient behavioral therapy smoking cessation groups. At a conservative estimate, therapy-uptake dropout after randomization will be 40% (cf. [83], 31% (*n* = 139) [84]; 34% (*n* = 406)). Additionally, studies suggest a loss to follow-up rate after starting the therapy of 20% ([85], 5% (*n* = 558) [86]; 6% (*n* = 1041) [87]; 14% (*n* = 2707) [88]; 19% (*n* = 220)). Thus, we expect a total dropout rate of 52%. The primary analysis will be conducted according to the intention-to-treat principle including participants who started the smoking cessation program. For this analysis, participants whose smoking status cannot be assessed will be classified as non-abstinent. Under these assumptions, observed abstinence rates are expected to be 22% versus 40%, respectively. Based on a two-sided χ^2^ test, a sample size of 137 participants per therapy group is necessary. Accounting for the assumed therapy-uptake dropout, a total of 458 participants (229 per group) will be randomized.

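### The 12-month cotinine cutoff makes no provision for users of nicotine replacement or e-cigarettes, so some non-smokers could be classed as smokers on a confirmatory endpoint

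*Protocol article*

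**What the plan says.** The Primary endpoint section under Measures defines abstinence by cigarettes: "participants will be classified as abstinent if they smoke no more than five cigarettes during the observation period". It adds biochemical verification at the later time point only: "abstinence will be validated by urine cotinine assessments at the 12-month follow-up". The one distinction it draws for cotinine is between first-hand and second-hand tobacco exposure.

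The section on biological specimens {33} gives the rule. Urine kits "will be sent to all participants stating that they have stopped smoking", and "a cutoff value of 250 ng/ml urine will be used as the baseline to identify active smokers". The stated reason for the cutoff is "To avoid misclassification of abstainers and passive smokers as actively smoking". Users of nicotine products are not mentioned.

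Other sections expect such users:

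- Intervention group: "participants receive advice on the use of stop-smoking aids and licensed medication to alleviate withdrawal symptoms". Use is voluntary.
- Aids for abstinence: lists nicotine patches, gums, sprays, sublingual tablets and other inhalants, and records use and its duration after therapy, at 6 months and at 12 months. It continues: "Additionally, the use of e-cigarettes will be evaluated". E-cigarettes are not primarily advised, but no section prohibits them, and a subgroup analysis of their users is planned.
- Discussion (limitations): counts e-cigarettes among the types of aid in the study.

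Statistical methods {20a} makes 12-month abstinence a confirmatory test at two-sided 5%, carried out if the 6-month test rejects. None of its sensitivity analyses (per-protocol, multiple imputation, all randomized) concerns cotinine-positive users of nicotine products.

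**The concern.** Cotinine is a metabolite of nicotine, whatever product the nicotine comes from. A participant who has smoked nothing but uses a patch, gum or a nicotine e-cigarette at 12 months meets the cigarette-based definition. If that participant's urine exceeds 250 ng/ml, the verification rule nevertheless identifies an active smoker. The protocol collects the information needed to recognise this person but never connects it to the cotinine result.

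The 12-month confirmatory comparison is at stake. If the affected share of abstainers is equal in the two arms, both observed rates shrink and power falls. If it differs, the odds ratio is biased, and the direction cannot be known in advance. Different use by arm is conceivable: one arm is a single team's programme, the other is delivered by many external therapists, and the Discussion accepts that their procedures may differ. Data analysts are not blinded ({17a}), which is a further reason to settle the classification before the data are seen.

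**Working it through.** **1. The plan's own figure.** Inputs from Sample size {14}: 22% versus 40% observed abstinence, two-sided 5%, power 90%. With the mean rate (0.22 + 0.40)/2 = 0.31:

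n = [1.960·√(2·0.31·0.69) + 1.282·√(0.22·0.78 + 0.40·0.60)]² / 0.18² = 136.6, so 137 per group.

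This agrees with the protocol. Allowing for 40% non-uptake, 137/0.6 = 228.3, so 229 per group, which also agrees. The planning is sound for what it covers; the point here is classification.

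**2. The classification, section against section.** Take a participant with no cigarettes, current nicotine-product use and cotinine above 250 ng/ml.

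- Under the Primary endpoint definition: abstinent.
- Under {33}: active smoker.
- Under the 12-month validation statement: abstinence not confirmed.

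Nothing in the protocol article resolves this.

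**3. Illustration of size.** Two assumptions are needed, because the protocol gives neither figure:

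- the 6-month planning rates also hold at 12 months;
- a share u of true abstainers in each arm is reclassified as smokers.

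Observed rates become 0.22·(1 − u_out) and 0.40·(1 − u_res). Power for n = 137 per arm, with p̄ the mean of the two rates, is

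Φ{ [ |p_res − p_out|·√n − 1.960·√(2p̄(1 − p̄)) ] / √(p_out(1 − p_out) + p_res(1 − p_res)) }.

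This is the χ² approximation used for the sample size; the planned Wald test should behave similarly.

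| u residential | u outpatient | Observed rates | Odds ratio | Power |
|---|---|---|---|---|
| 0% | 0% | 40.0% vs 22.0% | 2.36 | 90% |
| 5% | 5% | 38.0% vs 20.9% | 2.32 | 88% |
| 10% | 10% | 36.0% vs 19.8% | 2.28 | 85% |
| 15% | 15% | 34.0% vs 18.7% | 2.24 | 82% |
| 20% | 5% | 32.0% vs 20.9% | 1.78 | 55% |
| 10% | 20% | 36.0% vs 17.6% | 2.63 | 93% |

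Equal shares of this size cost a few points of power. Unequal shares matter more and can work either way: the odds ratio moves from 2.36 down to 1.78 in one row and up to 2.63 in another. The unequal rows show direction and sensitivity; they are not forecasts.

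**The case against.** Several points on the other side have force.

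- **No sentence says that a cotinine-positive participant is counted as relapsed.** The only explicit rule of that kind concerns loss to follow-up. The consequence follows from reading the endpoint and laboratory sections together, and a full protocol or analysis plan that is not shown may add a rule. This stands as a limit on the wording. It does not dispose of the point, because the article does fix a cutoff and its purpose, and as fixed it gives the wrong label to this group.
- **The number affected is unknown and may be small.** Aids are offered against withdrawal symptoms, their use is voluntary, and e-cigarettes are not primarily advised. Only users above 250 ng/ml are touched. The quality assessment of outpatient programmes also covers their recommendations on aids, which works against a difference between arms without guaranteeing equal use. All of this stands.
- **The power figures borrow 6-month rates.** The protocol claims no power for the 12-month test, so the figures above are not losses against a promised value.

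A reader might go further and infer an inflated false-positive rate: with no true difference (22% in both arms) and reclassified shares of 5% residential and 20% outpatient, a stand-alone 12-month test would reject about 11% of the time. The design does not support that as the trial's error rate. The 12-month test is confirmatory only after a 6-month rejection, and the 6-month endpoint uses no cotinine. With no effect at either time, the chance of a confirmatory 12-month claim cannot exceed the 5% of the 6-month test. A rate near 11% would require a real 6-month effect, rejected almost surely, that has vanished by 12 months.

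A reader might also treat "nicotine abstinence after 6 months as the primary endpoint of the trial" in {14} as evidence that nicotine users are meant to fail. That phrase occurs once, concerns the time point without a cotinine test, and does not displace the cigarette-based definition. It is a wording slip.

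**Conclusion.** The point holds for the 12-month endpoint. The verification rule in {33} and the cigarette-based definition give different answers for the same person, and the protocol foresees such people without saying which answer prevails. The 6-month endpoint, which is tested first and drives the sample size, is untouched.

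The size cannot be derived from the protocol. On the stated assumptions, power falls to between 88% and 82% for equal shares of 5% to 15%, and to about 55% in the unfavourable unequal case; other unequal shares would inflate the effect instead. The rule therefore cannot be defended as simply conservative.

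It would be too strong to say that the trial advises nicotine replacement and then penalises it. Participants receive advice on aids, use is voluntary, and e-cigarettes are merely not prohibited. This is a should-fix: a confirmatory endpoint is affected, but in an unknown number of participants, and the repair is simple.

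**What to change.** Before analysis, add to the 12-month endpoint definition that, for participants recorded as currently using nicotine replacement or e-cigarettes, cotinine above 250 ng/ml does not by itself overturn self-reported non-smoking. Add a sensitivity analysis that counts these participants as smokers, and tabulate their number by arm. In {14}, align the wording by writing smoking abstinence in place of nicotine abstinence.

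The cost is a few lines of text, one further analysis and one table; use of aids and e-cigarettes is already recorded at 12 months. The drawback is real. The protocol introduced cotinine because self-reports inflate abstinence, and under this rule claims by nicotine-product users remain unverified in the primary analysis. The sensitivity analysis bounds the effect of that. Which of the two classifications is primary is a judgement; the essential step is to fix it in advance and report both.

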### Statistical methods

#### Statistical methods for primary and secondary outcomes {20a}

A logistic regression model will be used to assess the efficacy of the therapy on the primary endpoint of abstinence after 6 months. The therapy effect will be tested using the Wald test at a two-sided significance level of 5%, and as an estimate of the effect size, the odds ratios will be given with 95% confidence interval. If the hypothesis of no therapy effect on abstinence after 6 months could be rejected, based on the closed test procedure, a confirmatory test of the therapy effect on abstinence after 12 months will be performed at a two-sided significance level of 5% using the same analysis. Additionally, the following sensitivity analyses will be performed. These will be per-protocol analyses including only participants who have completed the entire therapy and provided data on their smoking status. Furthermore, missing data on smoking status will be handled using multiple imputation methods [94]. Due to possible non-random therapy-uptake dropout in both randomized groups, possible group differences will be accounted for in additional sensitivity analyses including all randomized participants regardless of therapy uptake. In this analysis, non-starters will be categorized as smokers. Based on the assumed abstinence probabilities and assumed minimum therapy-uptake rates, this analysis would lead to observed 6-month abstinence rates of 13% versus 24%. With 229 randomized participants per group, this leads to a power of 85%. Secondary analyses will be conducted to assess non-compliance. Comparisons involve participant baseline characteristics of dropouts (non-starters and dropouts after the start of therapy) and compliers.

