##### Physical smoking dependence

The self-reported level of physical nicotine addiction will be assessed with the Fagerström Test for Nicotine Dependence (FTND [50]). The FTND is an internationally used economic questionnaire and comprises six items, including the quantity of cigarettes smoked and the degree of dependence or, rather, interference with daily routine. The sum score of four dichotomous items from 0 to 1 and two multiple choice items from 0 to 3 indicates the level of physical dependence from none or weak (0–2), medium (3–4), and strong (5–6) to very strong (7–10) physical dependence. The FTND has been shown to be predictive of successful smoking cessation; the higher the level of dependence, the lower the rate of abstinence [65].

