### Assignment of interventions: allocation

#### Sequence generation {16a}

Participants are randomized between therapy groups in a ratio of 1:1. Block randomization with randomly varying block size is performed based on computer-generated lists. Block sizes are documented separately from the study protocol in a document that is not accessible to investigators.

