#### Methods for additional analyses (e.g. subgroup analyses) {20b}

The prognostic effect of baseline characteristics (e.g. age, gender, socioeconomic status, smoking status prior to randomization, smoking-specific self-efficacy expectation) on smoking status and the predictive effect via interactions with the therapies will be evaluated in univariate and multivariate logistic regression models. If tests on interactive effects result in *p* < 0.05, the results will be presented in subgroups. No alpha adjustment for multiplicity in secondary analyses will be performed. Only the results of the primary endpoints abstinence after 6 and 12 months will be interpreted in a confirmatory manner. The *p* values from other analyses will be interpreted in a descriptive sense. All analyses will be conducted using SAS 9.4. The Clinical Trials Unit of the University Medical Center Freiburg will supervise data management and analyses.

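### The primary logistic model names only the therapy effect; adding baseline FTND, which the protocol calls predictive, would be a cheap improvement, mainly against imbalance among therapy starters

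*Protocol article*

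**What the plan says.** Section {20a} fixes the confirmatory analysis in some detail. It is a logistic regression for 6-month abstinence, in which "The therapy effect will be tested using the Wald test at a two-sided significance level of 5" per cent, and "as an estimate of the effect size, the odds ratios will be given with 95% confidence interval". If that test rejects, 12-month abstinence is tested in the same way. Therapy is the only term named.

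The surrounding sections point to an unadjusted comparison:

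- Sample size {14} uses a two-sided chi-squared test at 22% versus 40%.
- Sequence generation {16a} says "Block randomization with randomly varying block size is performed based on computer-generated lists" and names no stratification factor. The items sent to the randomisation office under {16b} include year of birth and sex but no dependence score.
- In {20b}, "The prognostic effect of baseline characteristics" is examined in separate univariate and multivariate models whose p values are read descriptively.

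The section on physical smoking dependence says "The FTND has been shown to be predictive of successful smoking cessation" and adds that higher dependence goes with lower abstinence.

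The primary set, under {14}, is restricted to participants who started the programme, with 40% assumed not to start. Section {20a} allows that this dropout may be non-random, and the Discussion gives differing effort between the arms as a reason.

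**The concern.** A baseline score that the protocol itself describes as predictive is used neither in the randomisation, as described, nor in the confirmatory model. Two things follow. A little power is forgone. More important, a difference in dependence between the arms would pass straight into the primary odds ratio.

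In an ordinary randomised comparison such a difference arises only by chance. Here the primary set is defined by an event after randomisation, namely starting therapy. If residential and outpatient therapy deter different kinds of smoker, the starters may differ systematically, and randomisation does not protect against that.

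**Working it through.** **Inputs from the protocol.** The test is two-sided at 5%, and the null "should be rejected with a power of 90" per cent. The control rate is "27% from outpatient smoking cessation under routine conditions are expected"; the alternative holds "if the residential program increases the abstinence probability to 50" per cent. Loss to follow-up after starting is 20%, counted as non-abstinent; non-uptake is 40%; allocation is 1:1.

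**Step 1: the plan's own figures.** Observed rates are 0.27 × 0.8 = 0.216 (stated as 22%) and 0.50 × 0.8 = 0.40. With pooled variance and no continuity correction, and a mean rate of 0.31:

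n = [1.960 √(2 × 0.31 × 0.69) + 1.282 √(0.22 × 0.78 + 0.40 × 0.60)]² / 0.18² = (1.282 + 0.822)² / 0.0324 ≈ 136.6, so 137 per group.

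Then 137 / 0.6 = 228.3, so 229 per group and 458 in total. Both figures match. Power at 137 per group is 90.1%. For the all-randomised sensitivity analysis (13% versus 24%, 229 per group) it is 86.0%, against the stated 85%.

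**Step 2: power gained by adjustment.** The protocol gives no effect size for FTND, so its strength is an assumption, varied from an odds ratio of 1.25 to 2.5 per SD. The two-sided 5% Wald test was simulated with and without one standard-normal baseline covariate: 137 per group, marginal rates fixed at 21.6% and 40%, 10,000 trials per setting. The marginal odds ratio is (0.40/0.60) / (0.216/0.784) = 2.42.

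| Assumed OR per SD | Power, unadjusted | Power, adjusted | Conditional OR |
|---|---|---|---|
| 1.25 | 91.1% | 91.3% | 2.44 |
| 1.5 | 91.5% | 92.3% | 2.49 |
| 2.0 | 91.4% | 93.7% | 2.63 |
| 2.5 | 91.6% | 94.9% | 2.78 |

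The gain is below 1 point for a weak or moderate predictor and 2 to 3 points for a strong one. In the all-randomised set (229 per group, 6,000 trials per setting), power goes from 86.8% to 87.4%, 86.6% to 87.1% and 86.1% to 88.4% at odds ratios of 1.25, 1.5 and 2.0. Type I error without imbalance stays near 5% in both models (4.7% to 4.8%).

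**Step 3: imbalance by chance.** With 137 per group, the difference in mean baseline score has standard error √(2/137) = 0.121 SD. A difference above 0.2 SD in either direction is 0.2/0.121 = 1.66 standard errors, which happens in about 10% of trials of this size.

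**Step 4: systematic imbalance among starters.** Both its size and the strength of FTND are assumptions. With 137 per group at 22% versus 40%, and residential starters the more dependent (4,000 trials per setting; a repeat with 10,000 agreed within 2 points):

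| Imbalance | OR per SD | Power, unadjusted | Power, adjusted |
|---|---|---|---|
| 0.2 SD | 1.5 | 82% | 90% to 92% |
| 0.2 SD | 2.0 | 79% | 90% to 92% |
| 0.3 SD | 1.5 | 80% | 90% to 92% |
| 0.3 SD | 2.0 | 71% | 90% to 92% |

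With no therapy effect (rate 30%), imbalance of 0.2 to 0.3 SD raises the unadjusted type I error to 6% to 7% (OR 1.5) or 8% to 11% (OR 2.0). Adjusted, it stays at about 5% to 6%. These results assume that the imbalance lies entirely in the measured score.

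**The case against.** The strongest reply is that the point is inferred from silence. Section {20a} never says that the model is unadjusted or contains therapy alone, and a condensed article may leave a covariate list to the analysis plan. That stands as a limit on certainty. But {20a} does fix the test, the effect measure, the hierarchy and the sensitivity analyses; the sizing is unadjusted; and {20b} keeps baseline characteristics in descriptive models. The fair reading is an unadjusted primary model.

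A second reply is that nothing stated is wrong. This also stands. A reader might infer that the trial is underpowered or that its sample size is faulty; Step 1 shows neither. An unadjusted comparison is valid under randomisation, although that defence fully covers only the all-randomised sensitivity analysis, not the starters-only primary set.

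A third reply is that the protocol already deals with uptake: an all-randomised sensitivity analysis, baseline comparisons of dropouts with compliers, and inclusion only of people willing to attend either therapy. It is also right that adjusting for a measured score does not restore the randomised comparison. A reader might take adjustment as a cure for selective uptake; it corrects measured imbalance only.

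Finally, the factual basis has limits. The measure descriptions give no time points for FTND or for the self-efficacy scale (SER), and the schedule figure is not shown. Trial design {8} places self-report assessment at baseline before randomisation, so baseline FTND is likely, but not confirmed. Nowhere does the article call SER predictive, so there is no equal case for requiring it.

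**Conclusion.** The point holds as a low-cost improvement, not as an error. As described, the confirmatory 6- and 12-month models name therapy only, while the article states that FTND predicts abstinence.

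It would be tempting to call this free power thrown away. The figures do not support that: the gain is about 0 to 3 points, it depends on an assumed predictor strength, and the design reaches 90% without it. The better reason is protection against measured imbalance in dependence. If starters differed by 0.2 to 0.3 SD, unadjusted power could fall to between 71% and 82%, or type I error rise to between 6% and 11%, with the adjusted analysis largely unaffected. The documents do not show that such an imbalance exists; they only concede that uptake may be non-random.

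**What to change.** In {20a}, before any analysis of outcomes, specify the 6- and 12-month primary models as therapy plus baseline FTND as a continuous score, after confirming that FTND is collected at baseline. SER may be added but is optional. Test the therapy term by the Wald test as planned.

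State a simple rule for missing baseline scores, for example filling in the overall baseline mean without regard to arm, so that no participant is dropped. Report the adjusted odds ratio, labelled as conditional, with a standardised risk difference and 95% confidence interval. Keep the unadjusted model as a sensitivity analysis, and retain the all-randomised analysis, which adjustment does not replace.

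The cost is a few sentences and, if baseline FTND is collected, no new data. There are two small downsides. The odds ratio changes meaning (2.42 marginal against 2.44 to 2.78 conditional over the assumed range), which the risk difference helps to keep readable. The change must also be dated and documented as an amendment, because 155 participants had been randomised at the version shown and {17a} says the analysts are not blinded.
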